## Abstract

**Background:**

In settings with high prevalence of female genital mutilation (FGM), the health sector could play a bigger role in its prevention and care of women and girls who have undergone this harmful practice. However, ministries of health lack clear policies, strategic plans or dedicated funding to implement anti-FGM interventions. Along with limited relevant knowledge and skills to prevent the practice of FGM and care for girls and women living with FGM, health providers have limited interpersonal communication skills and self-efficacy, while some may have supportive attitudes towards FGM and its medicalization. We propose to test the effectiveness of a health system strengthening intervention that includes training antenatal care (ANC) providers on person-centred communication (PCC) for FGM prevention.

**Methods:**

This will be a two-level, hybrid, effectiveness-implementation research study using a cluster randomized trial design in Guinea, Kenya and Somalia conducted over a 6 months period. In each country, within pre-selected regions/counties, 60 ANC clinics will be randomized to intervention and control arms. At baseline, all clinics will receive the level one intervention involving provision of FGM-related clinical guidelines and handbook as well as anti-FGM policies and posters. At month 3, intervention clinics will receive the level two intervention comprising of a training for ANC providers on PCC to challenge their FGM-related attitudes and build their communication skills to effectively provide FGM prevention counselling. A process evaluation will be conducted to understand ‘how’ and ‘why’ the intervention package achieves intended results. Multi-level regression modelling will be used for quantitative data analysis while qualitative data will be assessed using thematic content analysis to determine the effectiveness, feasibility and acceptability of the different intervention levels.

**Discussion:**

The proposed study will strengthen the knowledge base regarding how to effectively involve health providers in FGM prevention and care.

**Trial registration:**

Trial registration and date: PACTR201906696419769 (June 3rd, 2019).

**Supplementary Information:**

The online version contains supplementary material available at 10.1186/s12913-021-06097-w.

## Background

Female genital mutilation (FGM) is a harmful practice affecting more than 200 million women and girls aged 15–49 years globally [1, 2]. It involves the partial or total removal of external female genitalia or other injury to female genitals for non-medical reasons. FGM has no health benefits and interferes with the body’s natural functions [3]. Despite the elevated risk of health complications among those affected by this harmful practice, in settings with high FGM prevalence, the health workforce is neither actively engaged in prevention nor well trained to provide quality care for its complications. In addition, the absence of health sector policies and strategic plans or specified funding, presents a weak environment to implement prevention and care interventions [4, 5].

If countries are to achieve the Sustainable Development Goal (SDG) 5.3 to eliminate FGM by 2030, concerted efforts by all sectors are needed [6, 7]. Health providers not only play a key role in providing quality health care to women and girls suffering the negative consequences of FGM, but as highly respected members of society, they could also play the important role of being effective change agents contributing towards the abandonment of the practice. Nevertheless, there is limited evidence to guide the health sector in implementing effective prevention and care interventions at scale [7, 8]. The few studies conducted are considered to be of low quality and not informed by any behavior change theories.

Further, health providers in some of these settings have demonstrated attitudes supportive of FGM, promoting either its medicalization or continuation of some types considered to be ‘less harmful’ [5]. A formative study conducted by the World Health Organization (WHO) and partners in three regions of Guinea (Faranah, Labé and Conakry) to understand the health system response to FGM and its medicalization, revealed low coverage of training as well as poor knowledge, self-efficacy and interpersonal communication skills among Guinean health providers.

The formative research also highlighted the demand for additional training by health care providers as well as the potential role they could play in providing effective FGM prevention counselling. These findings informed the development of the intervention package and implementation strategy to be tested in this proposed study.

Several other activities have prompted and informed the development of the proposed study; the ongoing support by WHO for the development of national, FGM-related, health sector action plans highlighted the absence of evidence based effective health sector interventions to implement at large scale as well as the lack of a clear approach or methodology to provide FGM prevention or care within routine health services. Furthermore, there are limited training tools or aides to guide health care providers to provide prevention services; country-specific situational analyses on FGM epidemiology, national FGM abandonment strategies/interventions, current legislative and political positions as well as the status of health systems; review of effective health system interventions to address FGM within the health sector; review of existing interpersonal communication training materials and consultations with communication and behaviour change experts. Finally, we conducted a pilot exercise for the training package intervention with positive feedback from midwives reporting that it challenged their beliefs on what they considered a norm and felt empowered as change agents against this practice.

The proposed study will use a rigorous design to generate evidence on the effectiveness of a health systems strengthening approach to effectively address FGM. It is planned to be implemented on the low-level health care facilities that offer primary health care services within the three proposed countries. The proposed complex intervention package includes a novel training for ANC providers (nurses/midwives) that has been developed using existing behavior change theories. This training is aimed at improving their interpersonal communication skills and addressing their FGM-related attitudes and values [9, 10]. Though there is no evidence found on unintended harms resulting from health systems interventions, we will however remain vigilant in identifying, assessing and responding to any event as per study’s standard operating procedures. In light of the recent COVID-19 pandemic, we will implement safety measures during training and data collection activities in alignment with each country’s national guidance.

The proposed study will also involve a process evaluation component to explore ‘how’ and ‘why’ the intervention achieves its intended outcomes. Should this intervention prove to be effective, it has the potential to inform implementation of health sector strategies that will contribute meaningfully to achievement of the SDG 5.3 target.

## Study objective and specific AIMS

The objective of this implementation research study is to test the effectiveness of a two-level, complex intervention package in ANC clinics at the primary health care level in three sub-Saharan African countries namely, Guinea, Kenya and Somalia.

Specifically, the study aims to achieve the following:

Primary aims:
To determine if a health system strengthening (HSS) intervention within the ANC context improves preparedness to provide FGM prevention and care servicesTo determine if training ANC providers on person-centered communication (PCC) improves delivery of FGM prevention counseling for ANC clients in primary care settings

Secondary aims:
To determine if ANC providers who receive training on PCC for FGM prevention are more likely to have: 1) improved knowledge about FGM; 2) improved interpersonal communication skills; 3) improved self-efficacy and 4) less supportive attitudes towards FGM and its medicalizationTo understand ‘how’ and ‘why’ an intervention that uses a social norm change approach achieves its implementation outcomes, by measuring parameters such as fidelity, coverage, feasibility and acceptability of the delivered intervention

## Methods

The roles and responsibilities of all individuals and institutions involved in the study such as study staff, study investigators, steering committee, and the Data Safety and Monitoring Board (DSMB) are clearly described in the standard operating procedures.

### Study design

The proposed study is a hybrid, type-2, effectiveness-implementation research using a cluster randomized trial design [11]. The intervention being tested will involve a novel training for ANC providers to enable them to deliver person centered communication on FGM prevention while the health systems strengthening approach being evaluated includes making available health policies/directives, guidelines, posters and clinical tools which aims to prepare the health facility as an enabling environment for ANC providers to deliver FGM prevention and care services. A process evaluation will be conducted to explore ‘how’ and ‘why’ the intervention package achieves its intended results. The study design, methodology and analysis plan conform to the 2010 Consolidated Standards of Reporting Trial (CONSORT) checklist [12] while the proposed process evaluation conforms to the Consolidated Framework for Implementation Research (CFIR) recommendations [13].

The study interventions will target ANC clinics and ANC providers but will not affect the routine ANC services offered. Since we are proposing a dual testing of the effectiveness of a novel training and health systems strengthening approach, implementation of the study intervention components will follow a staggered approach (Fig. 1). The control and intervention arm will both receive Level one intervention which comprises of passive distribution of Ministry of Health directive or policy to health facilities on FGM prevention and care, WHO FGM clinical guidelines, clinical handbook on FGM and information and educational material in the form of posters to be hung to at the health facilities. The intervention arm will have ANC providers receive a novel person-centered communication training package on FGM prevention defined as the Level two intervention.

**Fig. 1 Fig1:**
[figure not shown]
Staggered intervention implementation

The Level one intervention will be initiated in both study arms at baseline (month 0) while the Level two intervention will be initiated at month 3 in the intervention arm only. The Level one intervention aims to improve health facility preparedness to provide FGM prevention and care services. It seeks to passively strengthen the health workforce knowledge and skills to provide treatment and care for FGM complications and to not perform FGM.

In contrast, Level two intervention is an active approach where ANC providers from the intervention sites will receive a novel training package that aims to strengthen their interpersonal communication knowledge, skills and self-efficacy to communicate in an effective, empathetic and sensitive way with their patients. The training package comprises of diverse participatory adult learning methods such as values clarification exercises; storytelling sessions; interactive games using visual training aids and handouts; and demonstrations and role plays which simulate a variety of clinical situations in which FGM is discussed as well as viewing and discussing an animated video which depicts the life of a midwife who becomes an advocate for change to end FGM.

These training activities aim to develop the person-centered skills of health care providers to enable them discuss beliefs about FGM during a clinical consultation, encourage self-reflection to challenge existent FGM beliefs and support and empower women to abandon the practice. During the training ANC providers will be trained on how to deliver a standardized “ABCD” approach for PCC i.e. “Assess” clients’ views on FGM, address and challenge their “Beliefs”, explore the possibility of “Change” and with client, “Decide” on the next steps to be taken. In doing so, it is anticipated that the patient will be empowered to own and move forward with her decisions. The delivery of this “ABCD” approach for PCC on FGM prevention will be one of the primary outcomes of the study.

### Conceptual framework

The proposed study recognizes that health care providers are key opinion leaders in their communities who are subject to the same social norms related to FGM and that they are positioned at the intersection between the health system and the community. The study, therefore, aims to strengthen the health system while also addressing community-wide, FGM-related cultural norms by targeting the ANC providers who are mainly nurses and midwives at primary health care level (Fig. 2).

**Fig. 2 Fig2:**
[figure not shown]
Conceptual framework/theory of change

### Theoretical framework

One of the aims of the proposed intervention package is to change the values and attitudes of ANC providers towards FGM using two underlying behavioral theories. These include the Conceptualization of Attitudes Theory [14], which states that individual-level attitudes are shaped through cognition (beliefs, thoughts and understanding of a particular concept), affect (feelings and values interpretation associated with a particular concept) and past experiences (one’s previous experiences regarding a particular concept). In this study, cognition and affect will be addressed by the training on PCC for FGM prevention that will focus on changing FGM-related attitudes/values and building ANC provider skills to deliver effective FGM prevention counselling. To understand the impact of external factors in shifting individual-level attitudes and behavior change, the Social Cognitive Theory has informed development of the intervention [15]. This is a social norm theory that addresses the way individuals are influenced by their society and the ways they can in turn, influence others around them.

### Study setting and population

#### Eligibility criteria

The proposed study will be conducted in three sub-Saharan African countries with reported high FGM prevalence. Population-based studies have shown that 98% of women and girls between 15 and 49 years in Somalia, 97% in Guinea and 21% in Kenya have undergone FGM, with 20 counties in Kenya having a prevalence of more than 80% [16]. Within each study country, 2–3 sub-national administrative units (regions/counties) have been purposively selected using the eligibility criteria below:
Regions/counties with FGM prevalence > 50% among females 15–49 years oldRegions/counties that have > 15 ANC clinics, seeing on average 30 new ANC clients/monthLogistical feasibility in terms of security and transport

### Sampling and randomization procedures

Randomization will be done at region/county level. All sampled ANC clinics will be paired based on average number of new ANC clients in November/December 2019, and then randomized into intervention and control arms on a 1:1 basis using STATA. The clinics will be blinded as to study arm allocation although ANC providers invited for the training on PCC for FGM prevention at month 3 may infer that their clinics are in the intervention arm. All ANC client participants will be blinded to study arm allocation of their ANC clinic.

For the process evaluation, sites will be selected based on responses from the month 3 data collection to identify sites that are complying with the level one intervention component. A convenience sample of six ANC providers and six new ANC clients from these clinics will be identified.

### Data collection

Data collectors in all countries will be trained by standardized training developed by WHO with WHO participation and supervision. Similarly, data collection will have regular supervision and monitoring. To ensure high participation, participating sites will be notified in advance on planned data collection dates. Data management with regards to data entry, coding, security, and storage, including any related processes to promote data quality are detailed in the study operations manual. Quantitative data will be collected at three time points in the intervention arm: baseline, month 3 and month 6; and at two time points in the control arm: baseline and month 6. All data collection will be conducted using structured questionnaires pre-programmed into hand-held tablets. Quantitative data collection instruments will include a screening tool for ANC providers to assess their socio-demographic information (SCR); a questionnaire assessing their FGM-related practices, skills, and attitudes (HCP); an exit questionnaire (EXT) administered to first ANC visit clients to assess their exposure to level one intervention components as well as their perception of and satisfaction with the ANC visit encounter as relates to counselling for FGM prevention provided through the ABCD approach (Table 2). All data collection tools will be translated into local languages, tested and validated in the three countries.

**Table 2 Tab2:** Respondents and data collection tools at different study time-points

Respondent	Data Collection Tool	# to be Interviewed	Time-Point
Cluster Randomized Trial			
ANC providers	**SCR Questionnaire**	30 in each arm	**Intervention:** Baseline **Control:** Baseline
	**HCP Questionnaire**	30 in each arm	**Intervention:** 0, 3, 6 months **Control:** 0, 6 months
New ANC clients	**EXT questionnaire**	300 in each arm	**Intervention:** 0, 3, 6 months **Control:** 0, 6 months
Process Evaluation			
ANC providers	**In-depth interviews**	6	6 months
New ANC clients	**In-depth interviews**	6	6 months
Health facility	**Health facility checklist**	30 in each arm	0, 3, 6 months

A health facility assessment will be conducted at baseline, month 3 and month 6 in both intervention and control arms using a health facility checklist (CHK), which will assess compliance to the level one intervention component using an observational checklist as well as a short set of questions for health facility managers. The observation will assess dose and fidelity of the level one intervention component. The questions for the facility managers will assess catchment population, number of ANC providers, number of ANC clients seen per month, as well as number of staff meetings and supervisory visits held. It will also assess the facility’s environmental context regarding any pro- or anti-FGM activities targeting its catchment population.

Qualitative data in the form of in-depth interviews (IDIs) among a convenience sample of ANC providers and first ANC visit clients will be conducted at month 6 in the intervention clinics as described above. The IDIs will explore the acceptability, feasibility and other motivational/de-motivational factors that might influence intervention implementation. The IDIs will also be used to explore acceptability and appropriateness of the intervention as well as assessing respondents’ agency, perceptions of service delivery and any perceived impact of PCC on their FGM-related values/attitudes. The IDIs will be guided by an interview guide (Supplementary File 1).

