To determine the impact of the Level one intervention component, changes from baseline to month 3 in the intervention arm will be analyzed (Fig. 3). Analysis of change from month 3 to month 6 in the intervention arm will be used to determine the impact of the training on PCC for FGM prevention. At month 6, comparison of study primary, secondary and intermediary endpoints between the intervention and control arms will assess the impact of the complete intervention package. Both crude and adjusted Odds Ratios (OR) will be presented.

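### The training effect is read from the month 3-to-6 change in the intervention arm alone, because provider and client interviews at month 3 skip the control arm

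*Protocol article*

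**What the plan says.** The Data collection section gives the intervention arm three rounds (months 0, 3 and 6), whereas the other clinics are covered only "at two time points in the control arm: baseline and month 6". Table 2 repeats this for both the provider questionnaire on FGM practices, skills and attitudes (HCP) and the client exit questionnaire (EXT): "Intervention: 0, 3, 6 months Control: 0, 6 months". Table 1 plans 900 intervention and 600 control clients per country.

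The facility checklist is the exception: "A health facility assessment will be conducted at baseline, month 3 and month 6 in both intervention and control arms".

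Under Study design, Level one starts in both arms at month 0, and "the Level two intervention will be initiated at month 3 in the intervention arm only".

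The Data analysis section gives three readings:
- the month 0-to-3 change in the intervention arm measures Level one;
- the month 3-to-6 change in the intervention arm measures the training;
- "At month 6, comparison of study primary, secondary and intermediary endpoints between the intervention and control arms" measures the complete intervention package.

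**The concern.** Whether the training improves counselling is a primary aim. The analysis the text assigns to that question is an uncontrolled before-after comparison inside a randomised trial. It is uncontrolled for the interview outcomes only because control clinics have no month-3 interviews. Anything else that raises FGM counselling between months 3 and 6, such as national activity, Level one continuing to take hold, or seasonal change in clients or staffing, would be counted as training effect. The article's own Discussion faults earlier studies for relying on pre- and post-test assessments without a comparison group.

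The unequal schedule has a second, smaller consequence. Before month 6, intervention providers have answered the FGM questionnaire twice and control providers once. Repeated questioning can itself prompt counselling or make the items familiar. The secondary outcomes (knowledge, attitudes, self-efficacy, communication) come from providers, and the primary counselling outcome also uses provider measures.

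**Working it through.** **1. The schedule is deliberate.** Sample size and Table 2 give 300 clients per arm per round. Intervention: 300 × 3 = 900. Control: 300 × 2 = 600. Total 1500. This matches Table 1 exactly, so the missing month-3 control round is planned and is not a typing slip.

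**2. What each contrast can show.**
- Months 0 to 3, intervention arm: Level one plus background trend. Controls also receive Level one at month 0, so month-3 control data would not supply an untreated comparator.
- Months 3 to 6, intervention arm: training plus background trend plus continuing Level one. No concurrent control for HCP or EXT.
- Month 6, between arms: Level one and trend are common to both arms and cancel. What remains is training plus the extra assessment round. It is therefore not the complete package, since both arms have had Level one.

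**3. Size of the trend problem.** From the document: 300 clients per round, 30 clinics, 10% non-response, hence 300 × 0.9 = 270 clients, 9 per clinic. Assumed: starting rate 30%, ICC 0.05, two-sided 5% test, no training effect, rounds treated as independent.

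Effective n = 270 / (1 + 8 × 0.05) = 192.9.

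P(declared improvement) = Φ[(d − 1.96·SE0) / SE1], where SE0 = √(2·p̄(1−p̄)/n), SE1 = √((p1(1−p1) + p2(1−p2))/n), p1 = 0.30, p2 = 0.30 + d, and p̄ is their mean.

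| Background rise d | SE0 | SE1 | ICC 0.05 | ICC 0 |
|---|---|---|---|---|
| 2 points | 0.0471 | 0.0471 | 6% | 7% |
| 5 points | 0.0477 | 0.0476 | 18% | 24% |
| 10 points | 0.0486 | 0.0483 | 54% | 68% |

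The SEs shown are for ICC 0.05. Without drift the figure is 2.5%. The same clinics appear in both rounds, so stable clinic differences would cancel and move the result towards the ICC 0 column.

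**4. Size of the assessment problem.** The document gives no figure. Assume 270 clients per arm, ICC 0.05 and a control rate of 10%, 20% or 30%. The SE of the month-6 difference is √(2p(1−p) × 1.4/270) = 0.031, 0.041 or 0.047. The false-positive rate is P(|Z + shift/SE| > 1.96):
- shift of 1 point: 5.5–6.2%;
- shift of 3 points: 10–17%;
- shift of 5 points: 19–37%.

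**5. Would a difference in change from month 3 be a better estimate?** Suppose the 300 month-3 exit interviews were spread over all 60 clinics: 5 per clinic, 150 per arm, 135 analysed (4.5 per clinic). Take a 10-point effect (q = p + 0.10), control rate p of 10–30% and ICC 0.05. Power = Φ(0.10/SE − 1.96).
- Month-6 contrast: SE² = [p(1−p) + q(1−q)] × 1.4/270, so SE 0.036–0.048 and power 79% down to 54%.
- Difference in change, clinic effects perfectly stable: SE² = 0.95 × {[p(1−p) + q(1−q)]/270 + 2p(1−p)/135}, so SE 0.046–0.067 and power 58% down to 32%.
- Difference in change, clinic effects independent between rounds: SE² = month-6 variance + 2p(1−p)(1 + 3.5 × 0.05)/135, so SE 0.054–0.077 and power 46% down to 25%.

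**The case against.** The strongest reply is that the trial already has a sound estimate of the training effect. Both arms are measured at baseline and month 6, only one is trained, and the sample size rests on a between-arm difference. This stands. A reader might infer that the staggered design cannot separate training from calendar trend at all. The documents do not support that: trend cancels in the month-6 contrast, and only the within-arm reading is exposed.

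A reader might also infer that month-3 control interviews would rescue the Level one analysis. They would not, because both arms receive Level one at month 0.

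On the extra assessment round, EXT respondents are new first-visit clients each time, so no client is re-interviewed. Any effect must act through providers and clinics. Both arms already have the baseline round, the Level one materials and the month-3 checklist visit. Neither direction nor size can be derived from the document. Shifts of 3 to 5 points would be 30–50% of the 10-point target difference, and a 1-point shift leaves the error rate close to nominal. It would go too far to call the month-6 test materially biased.

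Finally, the month-3 intervention round has stated uses: the two within-arm analyses and the choice of process-evaluation sites. Those explain why it is held in that arm. They do not justify reading its later change as the training effect. Fig. 3, which is not shown, and the full protocol may add detail, but the article's text states this attribution explicitly.

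**Conclusion.** The point holds for the within-arm month 3-to-6 analysis. As written, it attributes any background rise to the training. Under the stated assumptions (30% start, 270 clients per round, ICC 0.05, independent rounds, no training effect), a 5- or 10-point rise would pass as a significant improvement in about 18% or 54% of cases. The starting rate, ICC and drift are assumptions, not protocol figures.

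The assessment imbalance is real but secondary: one extra HCP round per intervention provider, of unknown effect, mainly relevant to provider-reported outcomes. The month-6 contrast is otherwise randomised, concurrent and free of calendar trend. It estimates the training plus that extra round, so describing it as the impact of the complete package is inaccurate. This is worth correcting and does not undermine the trial.

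**What to change.** 1. In Data analysis, name the between-arm month-6 comparison as the estimate of the training effect, adjusted for the baseline values already collected (at clinic level for client outcomes, since clients differ between rounds). Stop describing it as the effect of the complete package.
2. Label the within-arm 0-to-3 and 3-to-6 month changes as descriptive.
3. Give the HCP questionnaire to the 30 control providers per country at the month-3 checklist visit already planned in both arms. This balances provider assessment and gives provider outcomes a controlled 3-to-6 month change.

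Cost: items 1 and 2 need a text change only. Item 3 adds about 30 questionnaires per country (30 × 3 + 30 × 2 = 150 now, 30 × 6 = 180 after), with no new site visits, and an amendment to Table 2.

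Optional: spread the 300 month-3 exit interviews over all 60 clinics. Clients per country stay at 1500 (750 per arm), but the intervention arm's month-3 sample falls from 300 to 150, and Table 1 must change. A full month-3 control round instead would add 300 clients per country (1800 in total). With the spread sample, a difference in change from month 3 should be supportive only: its power is about 25–58%, against 54–79% for the month-6 contrast under the assumptions above.
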